### Blinding

Owing to the behavioral nature of the intervention conditions, blinding of participants and intervention personnel was not feasible. To minimize performance and detection bias, all sessions follow a standardized protocol with scripted instructions, and objective outcomes were obtained using instrument-based or computer-administered procedures (eg, fNIRS-derived hemodynamic responses and computerized cognitive tasks). Data processing and analyses will follow prespecified procedures.


## Results

### Trial Status

The study protocol was approved by the IRB of Nanyang Technological University (approval number: IRB-2023-939) and was funded by the Sendai University International Collaborative Research Grant (grant number: CER-2023) in April 2023. Recruitment and data collection were completed in December 2024. A total of 22 physically inactive university students were enrolled and allocated to either the S-C or the S-T arm, with outcomes compared against the corresponding modality-matched passive control condition (passive sitting for S-C and S-T). Data cleaning and preliminary analyses are ongoing, and the complete outcomes will be reported in a subsequent results paper (anticipated in late 2026).

### Methodological Substudy Results: MET Validation for Intervention Intensity

A methodological substudy was conducted to confirm that the two 5-minute activity modalities (S-C and S-T) meet the operational definition of LIPA (<3 METs), thereby justifying their classification for the main trial. The mean MET value was 0.98 during 5 minutes of quiet seated rest during the modality-matched passive control stage and 2.71 during S-C (paired *t* test, *P*<.05), indicating higher energy expenditure during S-C than during seated rest. Similarly, the mean MET value was 1.19 during 5 minutes of quiet standing and 2.26 during S-T (paired *t* test, *P*<.05), indicating higher energy expenditure during S-T than during quiet standing. As a safety check, paired-sample *t* tests showed no significant pre-post differences in BP or HR following either 5-minute bout. Collectively, these findings indicate that both 5-minute S-C and S-T bouts fell within the LIPA range (<3 METs) and could be implemented as brief, standardized LIPA breaks in the main trial. No analyses of the main trial outcomes (fNIRS-derived prefrontal cortex hemodynamics, cognitive performance, BP, subjective sleepiness, and back pain) are reported in this protocol paper; these results will be presented in a separate outcomes manuscript once analyses are finalized.

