### Study Objectives and Hypotheses

#### Substudy: Measurement of Oxygen Uptake in 5 Minutes of S-C and S-T and Intensity Validation

The objective of the substudy is to quantify oxygen uptake during a single 5-minute bout of S-C or S-T performed at a self-selected pace and to determine whether both modalities meet the operational definition of LIPA (<3 metabolic equivalents [METs]). We hypothesized that S-C against a negligible or minimal applied resistance and S-T at a self-determined cadence (about 2 seconds per full twist to the left and to the right) are LIPA-compliant and incur an energy output of <3 METs. Physical activities involving <3 METs are typically classified as LIPA. Data from an earlier study using the same S-C equipment showed that the intensity of S-C at a self-selected pace in older working adults is of light intensity [33]. Moreover, the use of waist-twisters at public outdoor parks are considered LIPA [35].

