### Study Setting and Participants

The trial was conducted at a university in Singapore. This manuscript is intended as a study protocol with trial status information, accompanied by supportive methodological evidence from a MET validation substudy. Prospective participants were students from the same university, aged between 21 and 30 years, who do not meet physical activity guidelines [36]. An a priori target sample size of 28 participants (n=14, 50%, per modality group) was estimated using G*Power 3.1 for a repeated-measures analysis with within-between factors (α=.05; 1 − β=0.80; Cohen f=0.25). Owing to recruitment constraints, 22 (78.6%) participants were ultimately enrolled (n=11, 50%, per modality group). This shortfall is acknowledged in the *Discussion* section as a limitation, with potential implications for statistical power, particularly for small-to-moderate effects. A suggested sample of 6 (27.3%) participants who met the selection criteria was recruited based on a G*power test (α=.05; power: S-C, 99%; S-T, 86%) for the substudy.

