### Protocol Design for the Substudy

A total of 6 (27.3%) participants for the substudy were drawn from the participant pool (N=22) for the main study. The 6 participants visited the exercise physiology laboratory on a designated day. Upon their arrival, a research team member explained the process to them. The participants were then allocated to either the S-C group or the S-T group, after which they spent approximately 5 minutes familiarizing themselves with either the S-C or the S-T equipment. During the indirect calorimetry measurement, a mouthpiece connected to a metabolic cart (Parvo Medics True One 2400) was attached to the participant’s head. The participant breathed through the mouthpiece while remaining seated for 5 minutes. The metabolic cart collected breath-by-breath expired air and recorded the rate of oxygen consumption (VO_2_) and METs. After baseline measurements were recorded, the participants rested for about 5 minutes. Subsequently, they underwent an indirect calorimetry session while doing S-C or S-T at a self-selected pace with minimal or negligible applied resistance for 5 minutes each. The total duration of the session averaged approximately 40 minutes. Figure 2 shows a schematic illustration of the substudy.

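### The sub-3-MET conclusion was tested only against rest, so light intensity is not demonstrated for sit-cycling by this substudy, and the number of participants per modality is unclear

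*Protocol article*

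**What the plan says.** The section on the substudy objective poses an upper-limit question: the substudy is "to determine whether both modalities meet the operational definition of LIPA (<3 metabolic equivalents [METs"]). The section on the MET validation results then gives four means: 0.98 at seated rest and 2.71 during sit-cycling; 1.19 in quiet standing and 2.26 during stand-twisting. Each pair is compared by a paired t test with P<.05, and the sit-cycling test is read as "indicating higher energy expenditure during S-C than during seated rest". The same section concludes that "these findings indicate that both 5-minute S-C and S-T bouts fell within the LIPA range (<3 METs"). The Abstract (Results) repeats this conclusion, and the Discussion (Summary) treats it as established.

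On numbers, Study Setting and Participants states "A suggested sample of 6 (27.3%) participants who met the selection criteria was recruited" on the basis of a "G*power test (α=.05; power: S-C, 99%; S-T, 86%) for the substudy". Protocol Design for the Substudy says "The participants were then allocated to either the S-C group or the S-T group", but then has participants measured "while doing S-C or S-T at a self-selected pace with minimal or negligible applied resistance for 5 minutes each". That section describes only a seated rest measurement, whereas the results compare stand-twisting with quiet standing.

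**The concern.** The hypothesis is that intensity lies below a ceiling. A paired test against rest shows only that activity costs more than resting; an activity averaging 4 METs could pass it equally well. The only evidence on the ceiling is therefore two point estimates without any measure of precision. For sit-cycling the estimate is 0.29 MET under the limit, in a very small sample working at a self-selected pace.

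At stake is the intensity label. The article says that the substudy justifies classifying both activities as light for the main trial, and the Discussion calls this step essential. If it is not demonstrated for sit-cycling, the main trial's results for that arm cannot be described without qualification as effects of light activity.

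**Working it through.** **Inputs.** Means are from the MET validation results: sit-cycling 2.71 (rest 0.98), stand-twisting 2.26 (rest 1.19). The threshold of 3 METs is from the substudy objective. n is 6 per modality if everyone did both, or about 3 if the 6 were split evenly; the article does not state the split. No SD is given, so SD is treated as unknown and a range is shown.

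**The article's own figures.** The powers of 99% and 86% cannot be reproduced, because no test, effect size, SD or sidedness is stated.

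**Step 1: what a demonstration below 3 requires.** The one-sided 95% upper limit of the mean is mean + t(.95, n−1) × SD/√n. Setting it equal to 3 gives the largest admissible SD = (3 − mean) × √n / t(.95, n−1), with t = 2.015 for n=6 and 2.920 for n=3.

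- Sit-cycling, n=6: 0.29 × 2.449 / 2.015 = 0.35
- Sit-cycling, n=3: 0.29 × 1.732 / 2.920 = 0.17
- Stand-twisting, n=6: 0.74 × 2.449 / 2.015 = 0.90
- Stand-twisting, n=3: 0.74 × 1.732 / 2.920 = 0.44

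**Step 2: what the reported tests require.** A two-sided paired test reaches P<.05 when the SD of the activity-minus-rest difference is below difference × √n / t(.975, n−1), with t = 2.571 for n=6 and 4.303 for n=3. The differences are 2.71 − 0.98 = 1.73 and 2.26 − 1.19 = 1.07.

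| Modality | n | Largest SD of activity METs for an upper limit below 3 | Largest SD of difference for P<.05 against rest |
|---|---|---|---|
| Sit-cycling | 6 | 0.35 | 1.65 |
| Sit-cycling | 3 | 0.17 | 0.70 |
| Stand-twisting | 6 | 0.90 | 1.02 |
| Stand-twisting | 3 | 0.44 | 0.43 |

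The two SD columns refer to different quantities, so they show orders of size and do not convert into each other. For sit-cycling the reported significance tolerates a spread more than four times what the ceiling allows, and so gives no assurance about the ceiling. For stand-twisting the two figures are close, and the margin to 3 is wider.

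**Step 3: sit-cycling upper limit over an assumed range of SD.**

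| Assumed SD (MET) | n=6 | n=3 |
|---|---|---|
| 0.2 | 2.87 | 3.05 |
| 0.3 | 2.96 | 3.22 |
| 0.4 | 3.04 | 3.38 |
| 0.5 | 3.12 | 3.55 |

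Whether the sit-cycling label passes depends on two quantities that the article does not give: the SD and the n per modality.

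**Step 4: n and rest state.** Allocation to one group or the other implies that the 6 were divided. The word *each* after the 5-minute duration, and one sample of 6 with a power for each modality, suggest that all 6 did both. No two numbers conflict; the wording admits both readings. The rest state for stand-twisting is seated in the methods and standing in the results.

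**The case against.** The article reads its t tests correctly, as showing a rise over rest, and the range statement can be taken to follow from the means, both of which are below 3. There is other support: the objective section cites an earlier study with the same chair at a self-selected pace, and the main trial used minimal resistance with exertion ratings every minute. An article condenses, so the SD and n may exist elsewhere. Much of this stands. The label has some support, and stand-twisting is little exposed. But the earlier study was in older working adults, exertion ratings are not METs, and the article presents a completed result whose only stated tests do not bear on the threshold.

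Three stronger readings are tempting and not supported.

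- *Sit-cycling actually reached 3 METs, or a large share of participants did.* Suppose the stated powers refer to a two-sided paired test against rest at the reported means. The implied SD of the sit-cycling difference is then 0.77 at n=6 or 0.31 at n=3. If that SD is also used as the SD of activity METs, the upper limit is about 3.35 or 3.23, and under normality about 35% or 17% of individuals are at or above 3. Each of these assumptions is outside the documents, and the share halves with the choice of n.
- *The stated powers are wrong.* Deriving effect sizes at n=6 and applying them to n=3 gives about 54% and 34%, but this presupposes n=6. At n=3, standardized effects of 5.58 and 3.62 would yield exactly the stated powers. No error is shown.
- *All conclusions of the main trial are undermined.* The primary endpoint compares the activity as delivered with passive control within person, and that contrast does not depend on the label.

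**Conclusion.** The concern holds in a limited form. The conclusion that both modalities are below 3 METs is not established by the analysis reported for it. For sit-cycling it would be established only with an SD of at most 0.35 MET (n=6) or 0.17 MET (n=3); for stand-twisting the limits are a more comfortable 0.90 or 0.44. These figures rest on the reported means, approximate normality and a one-sided 5% level. The right description for sit-cycling is *not demonstrated by this substudy*; it is neither refuted nor wholly without support. The n per modality and the rest state are ambiguous and need reconciling. The consequence is confined to the intensity label and to how the sit-cycling results are interpreted.

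**What to change.** For each modality, base the conclusion on a one-sample, one-sided comparison of activity METs with 3, reporting n, mean, SD and the one-sided 95% upper limit. Report the number of participants at or above 3 separately, as a description of individuals; a confidence limit for a mean says nothing about every participant.

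Reconcile Study Setting and Participants, Protocol Design for the Substudy and the MET validation results on n per modality and on the rest state used for stand-twisting. State which test and which n the 99% and 86% powers refer to.

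If the sit-cycling upper limit is 3 or more, write in the Abstract, the MET validation results and the Discussion summary: *sample mean below 3 METs; a mean of 3 METs or more is not excluded*. Carry that wording into the interpretation of the main trial.

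The cost is a small re-analysis of data already collected and possibly a weaker intensity statement for sit-cycling. The outcomes paper is anticipated in late 2026, so the correction can precede it.

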## Discussion

### Summary

This manuscript primarily serves as a study protocol with trial status information, detailing the rationale, design, procedures, and planned analyses for examining the acute effects of two 5-minute LIPA breaks (S-C and S-T) on neurocognitive and somatic outcomes among physically inactive university students. In addition, we reported findings from a methodological substudy undertaken to support the main trial by confirming that both S-C and S-T can be operationalized as LIPA (<3 METs). Taken together, this protocol provides a transparent framework for replication and for interpreting subsequent outcomes reporting from the main trial.

The primary aim of this protocol was to establish that a 5-minute bout of S-C or S-T constitutes LIPA. Consistent with our hypothesis, 5 minutes of both S-C and S-T were deemed as LIPA. These findings provide methodological support for the main study, which is designed to investigate the acute effects of LIPA on cognitive function and brain activity. Establishing the intensity of these modalities is an essential methodological step, as the primary trial aims to evaluate whether a brief LIPA bout can elicit measurable changes in prefrontal cortex hemodynamics and cognitive performance, alongside changes in subjective sleepiness and back pain. If effective, such short activity breaks may represent a pragmatic strategy to interrupt prolonged sitting in student populations who are at elevated risk of sustained sedentary exposure.

From a broader perspective, the importance of interrupting prolonged sitting, even among physically active individuals, has been emphasized [50]. In parallel, interventions using digital health technologies to reduce sedentary behavior in workplaces and to promote behavior change are gaining popularity [51]. Although much of the existing evidence on these digital interventions focuses on general health outcomes, evidence relating to brain activity and cognitive function remains limited. Research investigating how short physical activity breaks influence cerebral blood oxygenation and cognitive performance in adults is still in its infancy, and key parameters, such as the optimal exercise modality, bout duration, and interruption frequency, that are feasible in real-world settings are yet to be established. In this context, by integrating objective indices (eg, prefrontal cortex oxygenation) with behavioral and symptom-based outcomes (eg, working memory, inhibitory control, sleepiness, and back pain), this trial is expected to contribute to a more integrative understanding of how short, low-intensity movement may influence both neurocognitive and musculoskeletal-related indicators in young adults. Moreover, this protocol provides a practical framework to inform future studies seeking to elucidate whether brief S-C and S-T breaks, compared with prolonged sitting, can meaningfully reduce sedentary exposure and support cognitive functioning and overall well-being.

This protocol is underpinned by the MEF, which provides a robust foundation for understanding the multifaceted role of movement in health promotion. By valuing all movement behaviors, including LIPA, the MEF encourages a holistic approach to health that may be particularly relevant for university students, who are vulnerable to sedentary lifestyles [6,52].

### Strengths and Limitations

The strengths of this protocol include the pragmatic nature of the intervention (brief, low-cost, and implementable in common study settings), clearly specified eligibility criteria, standardized delivery of activity bouts, and prespecified outcome assessment time points. These features are intended to enhance transparency and reproducibility and to facilitate translation into real-world university contexts, such as classrooms, libraries, and other desk-bound study spaces.

A further strength of this protocol is the assessment schedule incorporating immediate and short-term follow-up. By evaluating outcomes at t_0_, t_1_, and t_2_, the study can differentiate transient responses from effects that persist for a meaningful period within a typical academic session, thereby improving interpretability and translational relevance.

Several limitations should be acknowledged when interpreting this protocol and the subsequent outcomes reporting. First, the achieved sample size (N=22) was smaller than the a priori target (N=28), which may reduce statistical power, particularly for detecting small-to-moderate effects. Accordingly, findings should be interpreted cautiously, with emphasis on effect sizes and Cis, in addition to statistical significance. Second, this is a nonrandomized study in which modality assignment followed a sequential (quasi-random) alternating schedule and allocation concealment was not implemented; therefore, a risk of selection bias cannot be ruled out despite consecutive enrollment and the use of a prespecified allocation schedule. In addition, because the protocol involves brief behavioral tasks assessed repeatedly over time, performance-related influences (eg, differential engagement, learning, or fatigue across repeated assessments) may affect outcomes, particularly for subjective measures, such as sleepiness and back pain. Third, blinding was not feasible for participants or intervention personnel due to the nature of the activity conditions, which may increase susceptibility to expectancy and performance effects, particularly for subjective outcomes, such as sleepiness and back pain. Although objective outcomes (eg, prefrontal cortex hemodynamics and computerized cognitive task performance) are relatively less susceptible to reporting bias, nonblinding may still influence participant engagement and effort during assessments. Fourth, although the analytical plan specifies a primary endpoint and prespecified multiplicity control for secondary outcomes, the assessment of multiple outcomes still warrants cautious interpretation to mitigate the risk of inflated type I errors. Finally, as the study was conducted within a single university context, generalizability may be limited.

### Future Directions

Future research should build on this protocol by implementing a fully randomized allocation procedure with allocation concealment; incorporating a sham or active control condition that better matches posture and expectancy; and recruiting larger samples, preferably across multiple sites, to improve precision and generalizability. In addition, preregistering a single primary endpoint (or a clearly ranked hierarchy of outcomes), applying a priori multiplicity control strategies, and considering linear mixed modeling approaches for repeated measures would further strengthen inferential robustness. Longer-term and ecologically embedded evaluations (eg, repeated breaks across a study day or semester) may also clarify whether acute responses translate into sustained benefits in cognitive performance and musculoskeletal symptoms.

## Abbreviations

BP: blood pressure
DLPFC: dorsolateral prefrontal cortex
fNIRS: functional near-infrared spectroscopy
GAQ: Get Active Questionnaire
Hhb: deoxygenated hemoglobin
HR: heart rate
IRB: Institutional Review Board
LIPA: light-intensity physical activity
LMM: large multimodal model
MEF: Movement Ecology Framework
MET: metabolic equivalent
MPA: moderate-intensity physical activity
NIR: near-infrared light
O₂Hb: oxygenated hemoglobin
OLBDQ: Oswestry Low Back Disability Questionnaire
RA: rating of alertness
RPE: rating of perceived exertion
S-C: sit-cycling
SCWT: Stroop Color and Word Test
SPIRIT: Standard Protocol Items: Recommendations for Interventional Trials
SSS: Stanford Sleepiness Scale
S-T: stand-twisting
VO2: oxygen consumption
VPA: vigorous-intensity physical activity
